## Methods

### Research Design

This research project comprises 2 studies resulting from an international collaboration between the Centre de recherche de l’Institut universitaire de cardiologie et de pneumologie de Québec (CR-IUCPQ, Université Laval, Canada), the Groupement des Hôpitaux de l’Institut Catholique de Lille (GHICL, France), and FormAction Santé (France). Study 1 (objective 1) is a prospective, multicentric, quantitative, and validation study realized in an outpatient hospital setting at the CR-IUCPQ and the GHICL. Study 2 (objectives 2 and 3) is a prospective, multicentric, mixed methods, and validation study realized at the participants’ homes in Québec (CR-IUCPQ) and in northern France (FormAction Santé).

### Participants and Inclusion and Exclusion Criteria

A quota sampling method, based on disease and sex (ie, 1:1), will be used. All sample sizes were calculated a priori with an open-source calculator available on the internet or SPSS (IBM) [23]. Inclusion and exclusion criteria are summarized in Textbox 1.

Inclusion and exclusion criteria.
**Inclusion criteria**
Adults ≥40 years oldDiagnosis of chronic obstructive pulmonary disease (Global Initiative for Chronic Obstructive Lung Disease Diagnostic Criteria 2 to 4) or of interstitial lung disease (>6 months)Clinically stable for ≥4 weeks
**Exclusion criteria**
Interstitial lung disease associated with connective tissue disease and sarcoidosis (often accompanied by multisystemic effects)Unstable or severe cardiac conditionInvalidating rheumatologic or neurologic conditionWeight exceeding maximal limits of exercise equipment (eg, 130 kg for the stepper)Any other physical or medical condition limiting or contraindicating exercise testingSimultaneous participation in another study requiring changes in medicationRecent pulmonary rehabilitation (≤1 year, potential learning bias for the 6-minute walk test and the 6-minute stepper test)For study 1 only: use of oxygen therapy (unable to provide oxygen therapy during testing due to limitation of gas exchange analysis equipment)For study 2 only: participation in study 1

For study 1, a mean difference of 0.28±0.32 L/min in maximal oxygen uptake between the 6MST and CPET was assumed, based on previous studies between the 6MWT and CPET [22,24]. To detect a difference of this amplitude with a paired sample *t* test, assuming a power of 80%, an α level of .05, and a dropout rate of 15%, 15 participants are needed. Fifteen individuals of each disease population (ie, COPD, n=15; ILD, n=15) will be included for a total sample of 30 participants (Québec, n=15; France, n=15), as cardiorespiratory responses to exercise are different among these populations [25].

For study 2, a minimal acceptable intraclass correlation coefficient of 0.5, and an expected intraclass correlation coefficient of 0.75, were assumed for the test-retest reliability of the 6MST. Assuming a power of 80%, an α level of .05, and a dropout rate of 15%, 52 participants (Québec, n=26; France; n=26) will be recruited. This calculated sample was taken as a whole, as test-retest reliability is not expected to be influenced by the type of respiratory disease.

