### Data Preparation and Analysis

All data will be stored in digital databases (REDCap [Research Electronic Data Capture] in Québec and OpenClinica in France) on secured servers at the participating research facilities (CR-IUCPQ and GHICL) following local protocols. Using a standardized thesaurus, research teams will enter data directly into both databases through remote access. With regard to data analysis, descriptive statistics will be used to summarize participant characteristics. For quantitative data, normality will be verified with Shapiro-Wilk tests and Q-Q plots. All statistical analyses will be completed using SPSS Statistics Version 28 (IBM) with a significance level set at *P*<.05. Graphical analyses will be conducted using Excel (version 2305; Microsoft Corporation) and qualitative analyses will be performed with Nvivio (version 14; Lumivero).

For objective 1, concurrent validity will be assessed using paired sample *t* tests (or Wilcoxon signed-rank tests) to verify whether peak cardiorespiratory (eg, oxygen consumption, minute ventilation, and heart rate) and symptomology (ie, dyspnea and leg fatigue) values obtained during the 6MST are comparable to the CPET and 6MWT. Pearson correlation coefficients (*r*) will also be calculated to quantify the strength of association between peak cardiorespiratory and symptomology values reached during the 6MST with those reached during the CPET and the 6MWT. Additional Pearson correlation coefficients (*r*) will be calculated to determine the strength of the association between the number of steps taken during the 6MST and peak oxygen consumption and heart rate reached during all 3 tests. The level of correlation will be interpreted as poor (≤0.20), fair (0.21-0.40), moderate (0.41-0.60), good (0.61-0.80), and very good (0.81-1.00) [41]. The agreement will be assessed with Bland-Altman plots and 95% limits of agreement (mean difference ± 1.96 SD of the difference) between peak cardiorespiratory and symptomology values reached during the 6MST and those reached during the CPET and the 6MWT [41].

For objective 2, reliability (trial 2 vs 3) will be assessed using paired sample *t* tests (or Wilcoxon signed-rank tests), Bland-Altman plots (with 95% limits of agreement), and intraclass correlations [42-44]. Intraclass correlations will be interpreted as poor (≤0.50), moderate (0.51-0.75), good (0.76-0.9), and very good (0.91-1.00) [44].

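### Study 2: a pooled COPD/ILD ICC need not hold within each disease, even if measurement error is the same in both; a disease-adjusted ICC should stand beside it

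*Protocol article*

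**What the plan says.** The sample-size paragraphs of the protocol article (end of Participants and Inclusion and Exclusion Criteria) set the study 2 target: "a minimal acceptable intraclass correlation coefficient of 0.5, and an expected intraclass correlation coefficient of 0.75, were assumed". They continue: "Assuming a power of 80%, an α level of .05, and a dropout rate of 15%, 52 participants". On disease they say "This calculated sample was taken as a whole", because "test-retest reliability is not expected to be influenced by the type of respiratory disease".

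The same section fixes the mix: "A quota sampling method, based on disease and sex (ie, 1:1), will be used".

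Under Data Preparation and Analysis, "reliability (trial 2 vs 3) will be assessed using paired sample" t tests or Wilcoxon tests, Bland-Altman plots with 95% limits of agreement, and intraclass correlations. The labels are also given there: "Intraclass correlations will be interpreted as poor (≤0.50), moderate (0.51-0.75), good (0.76-0.9), and very good (0.91-1.00". No split or adjustment by disease is mentioned. The hypothesis for objective 2 is that the ICCs will be good.

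Study 1, in contrast, is sized separately for COPD and ILD, "as cardiorespiratory responses to exercise are different among these populations".

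**The concern.** The reason given for pooling concerns how repeatable the test is in each disease. The ICC is not a measure of repeatability alone. It is between-patient variance divided by total variance, so it also depends on how spread out the patients are. When two diseases are pooled, any gap between their mean step counts counts as between-patient variance. The pooled ICC can then exceed the ICC in both diseases although measurement error is the same in each. The stated premise could be fully true and still not justify reading the pooled ICC as the value for COPD or for ILD.

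The ICC is the quantity on which study 2 is sized and by which reliability is labelled. A therapist tests one patient with one disease. If the pooled figure is quoted as the reliability of the test in COPD or in ILD, it may be too favourable.

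**Working it through.** **Inputs from the protocol article.** Minimal acceptable ICC 0.50; expected ICC 0.75; power 80%; α .05 (sidedness not stated); dropout 15%; N = 52; two trials compared (k = 2); disease mix 1:1; the good band starts at 0.76.

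**Assumed input.** d, the gap in mean steps between COPD and ILD, in units of the within-disease SD of a single trial. The document gives no value, so a range is shown. Variances are taken as equal in the two diseases.

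**1. The plan's own figure.** Walter-Eliasziw-Donner: n = 1 + 2k(z_α + z_β)² / [(k − 1)(ln C)²], with C = (1 + kθ₀)/(1 + kθ₁) and θ = ICC/(1 − ICC).

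- θ₀ = 0.50/0.50 = 1 and θ₁ = 0.75/0.25 = 3, so C = 3/7 and (ln C)² = 0.718.
- Two-sided α: (1.960 + 0.842)² = 7.849, so n = 1 + 4 × 7.849/0.718 = 44.7, that is 45.
- Dropout: 45 × 1.15 = 51.75, that is 52 (45/0.85 gives 53).

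N = 52 reproduces with two-sided α. One-sided α gives 36 before dropout and does not reproduce it.

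**2. Pooled ICC.** Set the within-disease variance to 1, so between-patient variance is ICC and error variance is 1 − ICC. In a 1:1 mix, a gap of d adds d²/4 to the between-patient variance and nothing to the error variance:

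ICC_pooled = (ICC + d²/4)/(1 + d²/4)

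Example, d = 1: (0.50 + 0.25)/1.25 = 0.60; (0.75 + 0.25)/1.25 = 0.80.

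| Within-disease ICC | d = 0 | d = 0.5 | d = 1 | d = 1.5 |
|---|---|---|---|---|
| 0.50 | 0.50 | 0.53 | 0.60 | 0.68 |
| 0.70 | 0.70 | 0.72 | 0.76 | 0.81 |
| 0.75 | 0.75 | 0.765 | 0.80 | 0.84 |

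**3. Gap needed to reach the good band (0.76).** Solving for d gives d = 2√[(0.76 − ICC)/0.24].

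- From 0.50: 2√(0.26/0.24) = 2.08.
- From 0.60: 2√(0.16/0.24) = 1.63.
- From 0.70: 2√(0.06/0.24) = 1.00.
- From 0.75: 2√(0.01/0.24) = 0.41.

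**4. Chance of concluding that the ICC exceeds 0.50 when the within-disease ICC is 0.50.** Completers: 52 × 0.85 = 44.2, so 44 pairs. Inverting the sample-size formula gives a probability of Φ(√[43(ln C)²/4] − 1.96).

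- d = 0.5: pooled ICC 9/17, θ = 1.125, C = 3/3.25. Φ(0.262 − 1.96) = 4.5%.
- d = 1: pooled ICC 0.60, θ = 1.5, C = 3/4. Φ(0.943 − 1.96) = 15.5%.
- d = 1.5: pooled ICC 0.68, θ = 2.125, C = 3/5.25. Φ(1.835 − 1.96) = 45%.

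A simulation (20,000 runs, F test, upper tail 0.025) gave 2.5%, 4.4%, 15% and 46% at d = 0, 0.5, 1 and 1.5.

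**5. What 22 completers per disease can support.** The exact F test of 0.50 against 0.75 has about 48% power in each disease. Full power in each would need about 53 recruited per disease, 106 in all.

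**The case against.** The strongest reply is that nothing in the document says step counts differ. A reader might infer a difference from the study 1 rationale, but that sentence concerns cardiorespiratory responses, and the step results quoted in the Background are correlations and a minimally important difference, not group means. With no gap there is no effect. Up to 0.5 SD the pooled ICC rises by at most 0.03. Eligible COPD spans grades 2 to 4, so within-disease spread may be wide and a gap of a full SD cannot be presumed. This stands, and it is why the size is given only as a range.

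Second, an ICC belongs to a population. The stated aim covers people with COPD or ILD, recruited 1:1, and for that mix the pooled ICC is the right value. It would be wrong to call it biased, or to call a rejection of 0.50 an error for the mixed population. The analysis section also specifies no test against 0.50; that value is a planning input. The percentages above therefore describe only what happens if the sizing test is applied and its result is read as a within-disease statement.

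Third, a reader might infer that only one ICC will be reported. The sentence on pooling justifies the sample size, and the analysis section neither commits to a single ICC nor excludes others. An analysis plan that is not shown may add them.

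Fourth, a reader might see studies 1 and 2 as contradictory. They are not: study 1 compares physiological responses and study 2 assesses repeatability, so different reasoning about disease is allowed.

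Finally, the paired t tests and Bland-Altman limits use within-person differences, so a gap in disease means does not affect them.

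None of this rescues the stated reason. Reliability that does not depend on disease, in the sense of equal measurement error, is not sufficient for the pooled ICC to describe each disease.

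**Conclusion.** The point holds as a limit on interpretation. The plan's reason for pooling does not support carrying the pooled ICC over to COPD or to ILD, and the article names no disease-adjusted ICC that would.

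The size depends entirely on d, which the document does not give. It is nil at d = 0 and small at 0.5 SD. At 1 SD it is material: the minimal acceptable value of 0.50 would appear as 0.60, and a moderate 0.70 would appear as a good 0.76. A within-disease ICC of 0.50 or 0.60 would need a gap of about 2.1 or 1.6 SD to be labelled good, so the plan should not be read as likely to turn poor reliability into good. The planning value of 0.75 lies just under the good band, so there a gap of 0.41 SD changes the label while the ICC moves by only 0.01.

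These figures assume a 1:1 mix, equal variances in the two diseases and 44 completers. N = 52 is not called into question.

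**What to change.** Keep the pooled sample and the pooled ICC, described as the value for a mixed COPD/ILD population. Beside it, estimate the ICC from a model with disease as a fixed effect, which removes the between-disease variance whatever its size. Use that value for any statement about reliability within COPD or within ILD. Report the ICC and the standard error of measurement for each disease with 95% CIs, labelled descriptive. State this before study 2 data are analysed; the Results section says study 2 recruitment follows completion of study 1.

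The cost is one model term and two rows in a table. No new data are needed and N stays essentially unchanged. The disease-adjusted ICC may be lower than the pooled one, and with about 22 completers per disease the separate intervals will be wide and cannot carry a confirmatory claim. If the diseases turn out to have similar mean step counts, the two ICCs will nearly agree and little is lost.

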### Study 1: Procedures and Measurements

For study 1, in addition to a review of medical records, two 3-hour laboratory visits (separated by 6-18 days) will be conducted. Participants will be instructed to take all medications as usual, including inhalers. A summary of collected data and outcomes is presented in Table 1.

**Table 1 table1:** Data collected during study 1.

Measurements		Medical records	Visit 1		Visit 2
**Sociodemographic**					
	Age	✓			
	Sex	✓			
	Pulmonary diagnosis	✓			
	Comorbidities and risk factors	✓			
**Anthropometric**					
	Mass (kg)		✓		
	Height (m)		✓		
	Composition (bioimpedance)		✓		
	Leg length (cm)		✓		
**Pulmonary function**					
	Spirometry		✓		
	Plethysmography		✓		
	DLCO^a^		✓		
**CPET^b^ on cycle ergometer**					
	Dyspnea (/10)^c^		✓		
	Leg fatigue (/10)^c^		✓		
	Absolute oxygen uptake (L/min)		✓		
	Relative oxygen uptake (mL/kg·min)		✓		
	Carbon dioxide excretion (L/min)		✓		
	Minute ventilation (L/min)		✓		
	Tidal volume (L)		✓		
	Respiratory rate (breath/min)		✓		
	Heart rate (bpm)		✓		
	Blood oxygen saturation (%)		✓		
	Blood pressure (mm Hg)		✓		
	Québec only: inspiratory capacity (pre and post)		✓		
**6MWT^a^**					
	Total distance traveled (m)			✓	
	Identical measurements as CPET			✓	
**6MST^e^**					
	Total number of steps			✓	
	Identical measurements as CPET			✓	

^a^DLCO: diffusing capacity of the lungs for carbon monoxide.

^b^CPET: maximal cardiopulmonary exercise testing.

^c^/10: modified Borg Scale rating.

^d^6MWT: 6-minute walk test.

^e^6MST: 6-minute stepper test.

#### Review of Medical Records

Medical records will be reviewed, and the information retrieved regarding participant sociodemographic characteristics will be age, sex, pulmonary diagnosis, medications, comorbidities, and cardiovascular risk factors. Physical activity level will be assessed using the Ricci and Gagnon questionnaire [26].

#### First Laboratory Visit

During the first laboratory visit, anthropometric measurements, pulmonary function tests, and CPET on a cycle ergometer will be performed.

#### Anthropometric Measurements

Anthropometric measurements will be composed of body mass, height, body composition (ie, lean and fat mass), and leg length. A standardized medical scale and stadiometer will be used to measure body mass and height, respectively. Body composition will be estimated by bioimpedance [27]. Leg length will be measured using a standard tape measure from the anterior superior iliac spine to the medial malleoli [28,29]. The mean of two measurements of the right leg will be used [28,29].

#### Pulmonary Function

Pulmonary function will be characterized by spirometry, lung volume assessment (plethysmography), and diffusing capacity of the lungs for carbon monoxide, following current guidelines [30-32]. Spirometry will be conducted first [30]. After a period of quiet breathing, participants will be instructed to inhale to total lung capacity and exhale quickly and forcefully to residual volume. Forced vital capacity and forced expiratory volume in 1 second will be recorded. The test will be repeated until an agreement of at least 5% is obtained for 3 measures of forced vital capacity. The mean values of these 3 tests will be recorded (forced vital capacity and forced expiratory volume in 1 second) [30]. Plethysmography will be conducted second [31]. Participants will be instructed to breathe quietly, hands on their cheeks, until end-expiratory lung volume is stable. The shutter will be closed near functional residual capacity, and participants will be instructed to conduct a series of gentle pants (between 0.5 and 1 Hz) in order to obtain at least 3 with adequate technique. The shutter will then be opened, and the participant will exhale to residual volume, followed by an inspiratory slow vital capacity maneuver. The test will be repeated until an agreement of at least 5% is obtained for 3 measures of functional residual capacity. The mean value of these 3 tests will be recorded (total lung capacity, slow vital capacity, inspiratory capacity, functional residual capacity, expiratory reserve volume, and residual volume) [31]. The diffusing capacity of the lungs for carbon monoxide will be measured third [32]. After a period of relaxed tidal breathing, participants will exhale slowly to residual volume, followed by a rapid inhalation to total lung capacity during which a standardized gas mixture will be provided (carbon monoxide, methane, oxygen, and nitrogen). Participants will be instructed to hold their breath for 8 to 12 seconds before exhaling to residual volume. The test will be repeated following a 4-minute rest period. At least 2 acceptable tests will be obtained [32].

#### Maximal Cardiopulmonary Exercise Testing

CPET will be performed on a cycle ergometer (Quinton Corival 400 in Québec and Ergoline Ergoselect 200 in France) in accordance with the current recommendations [33]. The protocol used is presented in Textbox 2. Briefly, following a warm-up, the work rate will increase by 10 to 15 watts per minute, following a ramp protocol, until the criteria for maximality is reached. The criteria for maximality will be those recommended by the American College of Sports Medicine and include abnormal cardiovascular responses or signs of ischemia, signs or symptoms of cerebral hypoxemia, marked pulsed blood oxygen desaturation (SpO_2_≤80%), and at the request of the participant [34]. Participants will be asked to maintain a pedaling rate of 60±5 revolutions per minute. The modified Borg scale (/10) will be used to assess dyspnea and leg fatigue at rest before the test, during (every 2 minutes and at peak exercise), and after the test (5 minutes following the end of the test). Cardiorespiratory responses during the CPET will be monitored continuously using a breath-by-breath gas analyzer (Oxycon Mobile in Québec and Metamax 3B Cortex in France), an electrocardiogram, and an oximeter (Nonin). This equipment will provide data for absolute and relative oxygen uptake, carbon dioxide excretion, minute ventilation, tidal volume, respiratory rate, heart rhythm and rate, and pulsed oxygen saturation (SpO_2_). Blood pressure will be measured manually before and after the test. In Québec only, inspiratory capacity will be measured before and within 10 seconds of the end of the test (sitting on the cycle ergometer and hands gripping the handlebars) and a reduction of more than 150 mL will confirm the occurrence of dynamic hyperinflation [35].

Protocol for CPET on the stationary cycle ergometer.

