**Monitoring**
Continuous: breath-by-breath gas analysis, electrocardiography, peripheral oxygen saturation (stop test if pulsed oxygen saturation ≤80% with symptoms, such as dizziness, nausea, etc)During the last minute of the unloaded phase, every 2 minutes during the incremental phase, immediately at completion, and at 5 minutes of the recovery phase: blood pressure, dyspnea (/10), and leg fatigue (/10)Pre- and postincremental phase (Québec only): inspiratory capacity

To address current international recommendations that require the test to be repeated twice, the first laboratory visit will end with a familiarization trial of the 6MWT for individuals who have not done the test during the previous 12 months (the 6MWT is routinely conducted during medical follow-ups in the centers in this study) [36,37]. Data from this familiarization trial will not be recorded (although vital signs will be monitored for safety).

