#### First Trial

The first trial of the 6MST (familiarization trial) will be conducted at the participant’s home with the therapist present. Preceding this trial, the Short Physical Performance Battery will be performed to obtain a general assessment of lower limb function [39].

The 6MST will be performed using a standardized portable stepper (same as in study 1) and following the same protocol as in study 1, including the 2-minute pretest warm-up period. However, full cardiorespiratory responses will not be measured. Instead, an oximeter (Nonin) will be used to monitor heart rate and SpO_2_ continuously. Blood pressure, dyspnea, and perceived exertion will be measured pre*-* and posttest using the modified Borg scale (/10). For individuals on home oxygen therapy, oxygen flows will be titrated if SpO_2_ falls below 88% during the test, with the aim of maintaining SpO_2_ between 88% and 92%, while always respecting the flow limits of the prescribing physician’s parameters. As in study 1, the test will be terminated if blood oxygen saturation falls to ≤80% accompanied by symptoms of hypoxia (such as dizziness, nausea, etc).

All adverse events will be recorded and graded according to the Common Terminology Criteria for Adverse Events, version 5 (United States Department of Health and Human Services), progressing from mild (1) to lethal (5) [40]. Textbox 5 presents the standardized grading used in this study. Adverse events are defined as any event that leads to (or could potentially lead to) prejudice to the participant or that inhibits the completion of the test. Examples include dyspnea, dizziness or nausea, close-call or fall events, musculoskeletal pain, chest pain, syncope, etc.

Classification of adverse events based on the Common Terminology Criteria for Adverse Events, version 5.

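### The CPET text and its protocol box disagree on the desaturation stop rule and on when blood pressure is measured

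*Protocol article*

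**What the plan says.** The section Maximal Cardiopulmonary Exercise Testing names Textbox 2 as the protocol used and then summarises it. In that summary the work rate rises "following a ramp protocol, until the criteria for maximality is reached". The listed criteria include abnormal cardiovascular responses or ischaemia, indications of cerebral hypoxaemia, and then "marked pulsed blood oxygen desaturation (SpO_2_≤80%), and at the request of the participant". The saturation item carries no symptom condition. On blood pressure the same section says: "Blood pressure will be measured manually before and after the test".

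The Monitoring part of Textbox 2 gives the desaturation rule as "stop test if pulsed oxygen saturation ≤80% with symptoms, such as dizziness, nausea, etc". It schedules blood pressure together with the Borg ratings: before the ramp, "every 2 minutes during the incremental phase", at completion, and at 5 minutes of recovery.

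In study 2, First Trial, the rule for the home stepper test reads: "As in study 1, the test will be terminated if blood oxygen saturation falls to ≤80% accompanied by symptoms of hypoxia".

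Under Data Preparation and Analysis, CPET peak values are the comparator for the 6MST in the paired tests, the correlations and the Bland-Altman limits.

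**The concern.** Two descriptions of one test should give the same instruction for the same event. Here a person at or below 80% saturation and free of symptoms meets the stopping criterion in the text and does not meet the one in the box. The population has moderate to very severe COPD or interstitial lung disease and is asked for a maximal effort, so the event is foreseeable.

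The stop rule also helps to set the reference value. Objective 1 expects 6MST peaks to be systematically lower than CPET peaks. Ending a ramp earlier can only leave peak oxygen uptake unchanged or lower it, so the choice of rule bears on the difference being estimated.

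The blood pressure conflict is a matter of safety monitoring. One description has no readings during incremental exercise and the other has several.

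**Working it through.** **Desaturation rule, side by side**

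| Place | Saturation | Symptoms required? |
|---|---|---|
| CPET running text | ≤80% | No; cerebral hypoxaemia is a separate item in the list |
| Textbox 2, Monitoring | ≤80% | Yes |
| Study 2, First Trial (6MST) | ≤80% | Yes, said to match study 1 |

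Because the text lists signs or symptoms of cerebral hypoxaemia as an item of their own, symptoms cannot be read into its saturation item. The cases split as follows:

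- ≤80% with symptoms: stopped under both descriptions.
- ≤80% without symptoms: stopped under the text; the stop condition in the box is not met.
- Above 80%: the saturation rule applies in neither.

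Only the middle case is affected. The study 2 sentence concerns the 6MST, so it supports the symptom version for the CPET only indirectly. The article states no separate desaturation rule for the study 1 6MST, so a reader who follows the cross-reference arrives at the CPET section and finds two versions there.

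**Blood pressure, side by side**

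The incremental phase lasts 8 to 12 minutes (Textbox 2). Readings during it:

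- Running text: 0.
- Box, every 2 minutes: 8/2 = 4 to 12/2 = 6.

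The text gives the Borg ratings a 2-minute schedule and blood pressure a before-and-after schedule, whereas the box puts both on one schedule. The box also refers to an unloaded phase, but the only exercise phase it lists before the ramp is a warm-up at 20 watts.

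**Possible size of the effect on peak oxygen uptake**

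The plan states no figure to reproduce. From the sample size paragraph: planned mean difference 0.28 L/min; 15 participants per disease group; 15% dropout, so 15 × 0.85 = 12.75, about 13 completers. The number of truncated tests (k) and the loss in peak uptake per truncated test (d) are assumptions; neither is in the document.

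Shift in the group mean difference = (k/13) × d

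| k | d (L/min) | Shift (L/min) | Share of 0.28 |
|---|---|---|---|
| 1 | 0.10 | 0.008 | 3% |
| 1 | 0.20 | 0.015 | 5% |
| 3 | 0.10 | 0.023 | 8% |
| 3 | 0.20 | 0.046 | 16% |

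The direction is fixed: under the earlier stop the CPET-6MST difference is the same or smaller. The size is not known.

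**The case against.** The strongest reply is that the article ranks its sources. It names Textbox 2 as the protocol used and introduces the prose as a brief summary, so assessors have one operative document. This makes the conflict closer to a drafting error than to two competing protocols. It does not remove it: brevity explains an omitted detail, not a different trigger for ending the test or a different measurement schedule.

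A second reply is that the box gives a condition for stopping and never orders staff to continue an asymptomatic participant at 80%. That is right. The two places are not literal opposite orders, and other criteria, including the participant's own request, may end the test anyway. Still, the stated conditions differ for the same event.

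A third is that the effect on the estimate is unproven. That also stands. Study 1 excludes people using oxygen therapy, which may make saturations of 80% less frequent.

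A reader might infer that the two centres will apply different rules and so build in a centre effect. The documents do not support that: neither centre is assigned its own rule, and divergence is only a possibility. A reader might also infer that tests stopped for safety will be analysed as verified maxima. The analysis section speaks of peak values reached and sets no such rule; the label in the text is loose, and no more than that can be shown.

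**Conclusion.** The point holds as an internal inconsistency on two items, and the stop rule is the more serious. It gives different stopping conditions for an asymptomatic participant at or below 80%, which is a safety ambiguity and can alter that participant's CPET peak. The illustrative shift of 0.008 to 0.046 L/min (3% to 16% of 0.28) rests wholly on assumed inputs and should not be read as an estimate of bias; in particular, the 16% is only the top of an assumed range.

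The blood pressure conflict is a safety-monitoring matter. It bears on peak values at most indirectly, in that exercise readings could inform the criterion of abnormal cardiovascular responses.

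Calling the list criteria for maximality is a secondary wording fault: the items named are reasons to end a test, and do not by themselves show maximal effort. Nothing here says which stop rule or which schedule is right.

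**What to change.** 1. The responsible clinicians reconcile the CPET text, Textbox 2 and the study 2 sentence into one clear desaturation stop rule, stating explicitly whether symptoms are required and to which tests it applies.
2. They reconcile the text and the box into one blood pressure schedule, and correct the name of the pre-ramp phase.
3. Both apply at both centres.
4. In the CPET text, the list is called criteria for ending the test.
5. Recruitment to study 1 began in February 2024, so the sponsor establishes which version was used in the tests already done.

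The cost is a short clarification to the protocol and test forms and a look back at completed tests. Recording the reason for ending each CPET, and repeating the CPET comparisons without tests ended by a safety criterion, would be useful. They are optional here, since an article may leave such details to the forms and the analysis plan.

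### The CPET desaturation stop is SpO2 ≤80% alone in the main text but SpO2 ≤80% with symptoms in Textbox 2, and the two must be reconciled

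*Protocol article*

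**What the plan says.** All three statements are in the protocol article.

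- **Maximal Cardiopulmonary Exercise Testing (main text).** The ramp is governed by this sentence: "the work rate will increase by 10 to 15 watts per minute, following a ramp protocol, until the criteria for maximality is reached". The list of criteria that follows includes "marked pulsed blood oxygen desaturation (SpO_2_≤80%), and at the request of the participant". The saturation item carries no symptom condition, and symptoms of cerebral hypoxemia are a separate item in the same list. The section also states "The protocol used is presented in Textbox 2".
- **Textbox 2, Monitoring.** For the same test the instruction is "stop test if pulsed oxygen saturation ≤80% with symptoms, such as dizziness, nausea, etc".
- **Study 2, First Trial.** For the home 6MST: "As in study 1, the test will be terminated if blood oxygen saturation falls to ≤80% accompanied by symptoms of hypoxia".

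Data Preparation and Analysis then uses the peak values from these tests. Paired tests are to verify whether peak cardiorespiratory and symptom "values obtained during the 6MST are comparable to the CPET and 6MWT", and correlations and Bland-Altman limits are computed on the same peaks.

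**The concern.** The two CPET statements share a threshold but not a condition, and they lead to opposite actions for one kind of participant: someone at or below 80% who reports no symptoms. The limit protects participants, so staff running the test need one version of it.

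There is also a measurement consequence. In an incremental test the stopping point determines the peak. If the ramp ends at the saturation reading, the recorded peak oxygen uptake, ventilation or heart rate may be lower than if the same participant had gone on. The main text calls its list criteria of maximality, so a test ended on saturation alone would also count as having met them. CPET is the reference test for objective 1, and the hypothesis is that 6MST values lie systematically below it. The rule that ends the reference test should therefore not depend on which paragraph is read.

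**Working it through.** No arithmetic settles this point. The check is a comparison of the texts.

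**Step 1: same test, same threshold.** The main text and Textbox 2 both concern the study 1 cycle-ergometer CPET, and both use SpO2 ≤80%.

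**Step 2: can the symptom condition be read into the main text?** No. The list already has its own item for signs or symptoms of cerebral hypoxemia. If the saturation item also needed symptoms, it would largely repeat that one. As written, saturation alone is enough.

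**Step 3: apply each desaturation statement to the two possible cases.**

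| Participant on the CPET | Main text | Textbox 2, Monitoring |
|---|---|---|
| SpO2 ≤80% with symptoms | stop | stop |
| SpO2 ≤80% without symptoms | stop | continue |

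The conflict lies entirely in the second row.

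**Step 4: does the third place settle it?** First Trial gives the with-symptoms version and presents it as carried over from study 1. The only place in study 1 where that version is printed is Textbox 2. The study 1 description of the 6MST gives no desaturation stop of its own. First Trial therefore agrees with Textbox 2 and disagrees with the main text, but it concerns the 6MST and does not say which CPET wording prevails.

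**Step 5: direction and size of the effect on the peaks.** The ramp rises by 10 to 15 W each minute, so ending it earlier can leave the peak unchanged or lower it. Putting a number on this would need (a) the share of participants who reach ≤80% without symptoms, (b) how long each would otherwise have continued, and (c) the oxygen uptake gained per added watt. The documents give none of these.

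**Step 6: could the difference come from the way the text was extracted, or from an amendment?** No. Both statements are complete sentences or clauses in the current text, and nothing marks either one as superseded.

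**The case against.** The strongest reply is that the document shows which text governs. The main text points to Textbox 2 as the protocol and then summarises it, and First Trial repeats the Textbox 2 version. On that view a condensed sentence dropped two words and the operative rule is clear. This has weight as to what was probably meant. It does not remove the conflict: the pointer suggests an order of precedence but does not state one, and the main-text list is itself introduced as what ends the ramp.

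A reader might also infer more than the documents support.

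- **Bias between sites.** Neither wording is assigned to a country. The section names site differences where they exist (ergometer, gas analyzer, inspiratory capacity in Québec only) and names none for stopping. Divergence between sites is possible but not shown.
- **A loss of power.** Study 1 is sized on a difference of 0.28±0.32 L/min, and one could subtract an assumed truncation from it. The result would run from negligible to severe depending on an unknown affected share. The affected group may be small, since study 1 excludes oxygen users ("For study 1 only: use of oxygen therapy"). The 0.28 is also borrowed from earlier 6MWT–CPET studies whose stopping rules are not shown, so it may already contain such an effect.
- **A need for one identical rule across CPET, 6MWT and 6MST.** Under Textbox 2, the CPET and the only stated 6MST stop already agree. No saturation stop is stated for the study 1 6MWT, which is referred to its own recommendations. Asking for a common rule would be a clinical proposal, not a reconciliation of conflicting text.

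**Conclusion.** The contradiction stands and should be corrected: two current statements of the CPET desaturation stop give opposite instructions for a participant at ≤80% without symptoms. This conclusion rests on the wording alone and needs no assumption about frequency. It matters first as an ambiguous safety limit. Second, it is a possible and unquantified influence on the CPET peaks set against the 6MST. The documents do not support a figure for lost power, and they do not show that the sites will differ. No view is taken here on which wording is clinically right.

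**What to change.** Reconcile the main text of Maximal Cardiopulmonary Exercise Testing, Textbox 2 (Monitoring) and the study 1 cross-reference in First Trial, so that the CPET desaturation stop is stated once and the other places refer to it. The clinical team decides its content. Both sites then work from that wording. As study 1 has been recruiting since February 2024, it would also help to note which wording was used for CPETs already done.

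An optional, low-cost addition is to record the reason each study 1 test ended and to repeat the 6MST–CPET comparison without CPETs ended for desaturation. If the full protocol or analysis plan already provides for this, nothing more is needed.

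The cost is one wording correction and a note to both sites, plus one data field and one sensitivity analysis if the option is taken. No extra participants are required.
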